## Supplementary information

| Contents                                                                                                                                                                                | Page |
|------------------------------------------------------------------------------------------------------------------------------------------------------------------------------------------------|-------------|
| Supplementary Table 1. Seroconversion rates to co-purified DTaP or DT before and day 28 after vaccination based on subgroups that were positive or negative for antibodies at baseline. | 2           |
| Protocol                                                                                                                                                                                | 3-18        |
| CONSORT 2010 checklist                                                                                                                                                                  | 19-20       |

**Supplementary Table 1.** Seroconversion rates to co-purified DTaP or DT before and day 28 after vaccination based on subgroups that were positive or negative for antibodies at baseline.

| Baseline antibody | co-purified DTaP |              | DT  |              | P |
|-------------------|------------------|--------------|-----|--------------|----------|
|                   | N                | Rate, n (%)  | N   | Rate, n (%)  |          |
| anti-PT    |                  |              |     |              |          |
| ≥20 IU/ml         | 21               | 11(52.38)    | 8   | 0(0)         |          |
| < 20 IU/ml        | 213              | 179 (84.04)  | 216 | 5 (2.31)     |          |
| anti-FHA   |                  |              |     |              |          |
| ≥20 IU/ml         | 85               | 31 (36.47)   | 69  | 0(0)         |          |
| < 20 IU/ml        | 149              | 143 (95.97)  | 155 | 8 (5.16)     |          |
| anti-DT    |                  |              |     |              |          |
| ≥0.1 IU/ml        | 87               | 87 (100.00)  | 77  | 77 (100.00)  | 1.000    |
| < 0.1 IU/ml       | 147              | 147 (100.00) | 147 | 147 (100.00) | 1.000    |
| anti-TT    |                  |              |     |              |          |
| ≥0.1 IU/ml        | 214              | 207 (96.73)  | 203 | 174 (85.71)  | <0.001   |
| < 0.1 IU/ml       | 20               | 20 (100.00)  | 21  | 21 (100.00)  | 1.000    |

The two-sided  $\chi^2$  test or Fisher's exact test to compare seroconversion rates between arms. anti-PT, anti-pertussis toxin antibody; anti-FHA, anti-filamentous hemagglutinin antibody; anti-DT, anti-diphtheria antibody; anti-TT, anti-tetanus antibody; co-purified DTaP, co-purified diphtheria, tetanus and acellular pertussis combined vaccine; DT, diphtheria and tetanus combined vaccine.

**A randomized, controlled, clinical trial of the booster dose of co-purified diphtheria, tetanus and acellular pertussis combined vaccine (co-purified DTaP) or diphtheria and tetanus combined vaccine (DT) at Children Aged 6 Years**

Registration Class: Prophylactic biological product

Clinical Phase: IV

Protocol No.: DTaP/DT-2023-02

Version No.: 1.0

Version Date: April 17, 2023

Sponsors (seal): China National Biotec Group Company Limited

Chengdu Institute of Biological Products Co., Ltd.

Wuhan Institute of Biological Products Co., Ltd.

Research Institutions: Zhejiang Provincial Center for Disease Control and Prevention

## PROTOCOL SYNOPSIS

|                                      |                                                                                                                                                                                                                                                                                                                                                                                                                                                                                                                                                                                                                                                                                                                                                                                                                                                                                                                        |
|--------------------------------------|------------------------------------------------------------------------------------------------------------------------------------------------------------------------------------------------------------------------------------------------------------------------------------------------------------------------------------------------------------------------------------------------------------------------------------------------------------------------------------------------------------------------------------------------------------------------------------------------------------------------------------------------------------------------------------------------------------------------------------------------------------------------------------------------------------------------------------------------------------------------------------------------------------------------|
| Protocol Name                 | A randomized, controlled, clinical trial of the booster dose of co-purified diphtheria, tetanus and acellular pertussis combined vaccine (co-purified DTaP) or diphtheria and tetanus combined vaccine (DT) at Children Aged 6 Years                                                                                                                                                                                                                                                                                                                                                                                                                                                                                                                                                                                                                                                                                   |
| Product Features              | 
(1) Co-purified diphtheria, tetanus and acellular pertussis combined vaccine (co-purified DTaP) is made of acellular pertussis vaccine stock solution, diphtheria toxoid stock solution and tetanus toxoid stock solution plus aluminum hydroxide adjuvant. It is a kind of white or light yellow suspension. After placing, the adjuvant sinks and shakes to form a uniform suspension. Contain appropriate amount of thiomersal bacteriostatic agent.
 
(2) diphtheria and tetanus combined vaccine (DT) made from diphtheria toxoid stock solution and tetanus toxoid stock solution plus aluminum hydroxide adjuvant. It is a milky white uniform suspension. The adjuvant should be placed for a long time to sink. The upper layer of the solution should be colorless and clear, but it can be evenly dispersed after shaking, containing an appropriate amount of thiomersal bacteriostatic agent.
 |
| Indications /Study Population | 
The co-purified DTaP is applicable to children aged 3 months to 6 years.
 
The DT is applicable to children under 12 years of age.
                                                                                                                                                                                                                                                                                                                                                                                                                                                                                                                                                                                                                                                                                                                                                                         |
| Study Objective               | The safety and immunogenicity of fifth dose of co-purified DTaP against pertussis in 6-year-old children.                                                                                                                                                                                                                                                                                                                                                                                                                                                                                                                                                                                                                                                                                                                                                                                                              |
| Study Design                  | 
This trial uses a randomized, controlled, open-label design to evaluate the safety and immunogenicity of the booster dose of co-purified DTaP or DT at children aged 6 years.
 
This study plans to enroll 480 subjects who will be randomized into 2 groups with 240 subjects per group.
 
Grouping:
 
Study group is the co-purified DTaP group: The target number of
                                                                                                                                                                                                                                                                                                                                                                                                                                                    |

|                   |                                                                                                                                                                                                                                                                                                                                                                                                                                                                                                                                                                                                                                |
|-------------------|--------------------------------------------------------------------------------------------------------------------------------------------------------------------------------------------------------------------------------------------------------------------------------------------------------------------------------------------------------------------------------------------------------------------------------------------------------------------------------------------------------------------------------------------------------------------------------------------------------------------------------|
|                   | 
enrollment is 240. Blood samples will be collected before immunization on D0 and the subjects will then be vaccinated with the co-purified DTaP (0.5 mL/vaccine); blood samples will be collected on D28.
 
Control group is the DT group: The target number of enrollment is 240. Blood samples will be collected before immunization on D0 and the subjects will then be vaccinated with the DT (0.5 mL/vaccine); blood samples will be collected on D28.
                                                                                                                                                        |
| Hypotheses | 
1.The seroconversion rate of pertussis antibody in 6-year-old children vaccinated with co-purified DTaP vaccine is not less than 70%.
 
2. There was no significant difference in the seroconversion rates of diphtheria and tetanus antibodies between 6-year-old children vaccinated with co-purified DTaP vaccine and DT.
                                                                                                                                                                                                                                                                                       |
| Vaccines   | 
Vaccine 1: co-purified DTaP
 
Manufacturer: Chengdu Institute of Biological Products Co., Ltd.
 
Strength: 0.5 mL/vial/dose, the titer of acellular pertussis vaccine, diphtheria vaccine and tetanus vaccine shall not be lower than 4.0 IU, 30 IU and 40 IU respectively.
 
Vaccine lot no.: 20220311
 
Vaccine 2: DT
 
Manufacturer: Wuhan Institute of Biological Products Co., Ltd.
 
Strength: 0.5 mL/vial/dose, the titer of diphtheria toxoid is not less than 30IU; the titer of tetanus toxoid should not be lower than 40IU.
 
Vaccine lot no.: 202112020-2
 |
| Duration   | The entire clinical trial lasts about 18 months                                                                                                                                                                                                                                                                                                                                                                                                                                                                                                                                                                                |

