#### **Immunogenicity assessment criteria for pertussis vaccine:**

Positive: Antibody titer is  $\geq 0.1$  IU/mL.

Seroconversion: Antibody concentration is  $< 0.1$  IU/mL before immunization and  $\geq 0.1$  IU/mL after immunization; or antibody concentration is  $\geq 0.1$  IU/mL before immunization and is increased  $\geq 4$ -fold after immunization.

Antibody level: Geometric mean concentrations (GMCs) of serum antibody before and after pertussis vaccine immunization as well geometric mean increase (GMI) in serum antibody after immunization.

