### 3.7 Sample Size Estimation

The sample size was estimated using an objective performance criteria method. Assuming the target value was 70% of the seroconversion rate of anti-pertussis in the co-purified DTaP group after vaccination, with a two-sided  $\alpha$  of 0.05, a power of 90%, and a potential loss to follow-up of 15%, we estimated at least a sample size of 240 participants per group.

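### Hypothesis 1 sets one pertussis antibody rate against 70%, but anti-PT and anti-FHA are scored separately, and the plan does not say which decides or whether the point estimate or a confidence limit is judged

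*Combined protocol and SAP*

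**What the plan says.** The pertussis claim is set out in five places.

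- **Synopsis, Hypotheses.** Hypothesis 1 is "The seroconversion rate of pertussis antibody in 6-year-old children vaccinated with co-purified DTaP vaccine is not less than 70" (per cent). It concerns one antibody and one rate, and no test or confidence limit is mentioned.
- **Section 1.1.** The primary outcomes include seroconversion and seropositive rates of anti-pertussis antibodies in the DTaP group. The wording is plural, but no antigen is named.
- **Section 3.3.** Under "Immunogenicity assessment criteria for pertussis vaccine" there is one undivided definition with a cut-off of 0.1 IU/mL. The ELISA sentence also says only pertussis.
- **Section 3.7.** "The sample size was estimated using an objective performance criteria method", and the "target value was 70% of the seroconversion rate of anti-pertussis in the co-purified DTaP group after vaccination". The test is two-sided at 0.05 with 90% power and 15% loss to follow-up, and "we estimated at least a sample size of 240 participants per group".
- **Supplementary Table 1.** Two pertussis antibodies, anti-PT and anti-FHA, each have their own seroconversion counts, split by baseline level at 20 IU/ml.

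**The concern.** A single hypothesis needs a single decision rule. Here one target faces two measured responses, and two choices are left open: which antigen (or both) must reach 70%, and what reaching 70% means. If the two responses fall on different sides of the chosen criterion, the unwritten rule determines the trial's pertussis conclusion. Pertussis is the stated study objective, and Hypothesis 1 is the only hypothesis about it. With no rule on paper, the choice could be made once the titres are known. A result supported by one antigen could then be worded as a result for pertussis as a whole.

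**Working it through.** **1. The plan's own figure.** Section 3.7 gives p0 = 0.70, two-sided alpha 0.05, power 90%, loss 15% and N = 240 per group. It gives no expected rate p1, so 240 cannot be reproduced from its own inputs. Assuming p1 = 0.80:

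n = [z(0.975)·√(p0·q0) + z(0.90)·√(p1·q1)]² / (p1 − p0)²
= [1.960·√0.21 + 1.282·√0.16]² / 0.10² ≈ 199.1, rounded up to 200; 200/0.85 ≈ 235.3, rounded up to 236.

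This is close to 240. The result depends strongly on p1: 0.75 gives 995, 0.79 gives 293 and 0.85 gives 97. What matters here is that the calculation is a formal test of one rate against 70%. It does not provide for two antigens.

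**2. Counts, DTaP arm, Supplementary Table 1 (baseline strata summed).**

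- Anti-PT: 11 of 21 plus 179 of 213 = 190/234 = 81.2%.
- Anti-FHA: 31 of 85 plus 143 of 149 = 174/234 = 74.4%.

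**3. Judged by the point estimate.** Both 81.2% and 74.4% exceed 70%, so both antigens meet the target.

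**4. Judged by the lower two-sided 95% limit.** The exact (Clopper-Pearson) limits are the 0.025 quantile of Beta(x, n − x + 1) and the 0.975 quantile of Beta(x + 1, n − x).

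| Antigen | x/n | Rate | Exact 95% CI | Exact two-sided p against 70% |
|---|---|---|---|---|
| Anti-PT | 190/234 | 81.2% | 75.6 to 86.0 | 0.0001 |
| Anti-FHA | 174/234 | 74.4% | 68.3 to 79.8 | 0.154 |

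With n = 234, the lower limit exceeds 70% only from 178 responders (76.1%). Anti-FHA has 174, four short.

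**5. Sensitivity to the interval method.** Across the Wald, Wilson, exact, Agresti-Coull and Jeffreys methods, the lower 95% limit is 75.6 to 76.2% for anti-PT and 68.3 to 68.8% for anti-FHA. Even the 90% interval for anti-FHA starts at 69.2 to 69.7%. The split does not depend on the method, or on one-sided 0.025 versus 0.05.

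**6. What each rule gives under the lower-limit reading.**

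- Anti-PT decides: met.
- Anti-FHA decides: not shown.
- Both required: not shown.
- Either suffices: met through anti-PT, including at a Bonferroni one-sided 0.0125 (one-sided p = 0.00007).

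**The case against.** The strongest reply is that Hypothesis 1 says only that the rate is not less than 70%. Read literally, both antigens satisfy it. A reader might infer from the intervals that the two antigens give opposite verdicts whatever rule is used, or that the anti-FHA rate falls short of 70%. The documents support neither. The split appears only under a lower-limit rule, which is inferred from the alpha and power in section 3.7 and is not written as a criterion. Even then the anti-FHA interval contains 70%, so that result is inconclusive and is not evidence of a lower rate.

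Four further objections stand in part.

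- The counts are not seroconversion as section 3.3 defines it. The table uses 20 IU/ml for anti-PT and anti-FHA, section 3.3 gives 0.1 IU/mL for pertussis, and the table names no analysis set although the per-protocol set is primary. The counts therefore illustrate the consequence. The missing rule remains under any cut-off.
- The plural in section 1.1 suggests separate reporting by antibody, which is what the table does. Separate reporting does not settle which result decides Hypothesis 1.
- A reader might add child-level composites to the possible readings. The plan defines none, so they are left out here. Nor do the documents show that a single-antigen result was presented as an overall pertussis result: the table names both antibodies.
- Some protocol pages were not available, including whatever lies between sections 1.2 and 3. The absence of a rule can be asserted only for the available text. That text does include the hypotheses, objectives, criteria, sample size and analysis sets, where a rule would be expected.

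Nothing in the documents makes requiring both antigens the only acceptable rule. Naming one primary antigen in advance would also remove the ambiguity.

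**Conclusion.** The concern holds in conditional form. In the available text, the plan neither names the pertussis antigens nor says which one decides Hypothesis 1, and it does not say how the 70% is judged. If the lower two-sided 95% limit is the criterion, anti-PT clears the target by 5.6 percentage points (75.6% against 70%), while the anti-FHA lower limit lies 1.7 points below it (68.3%). The conclusion about pertussis as a whole then depends on a choice the plan does not make. If the point estimate is the criterion, both antigens pass and the choice of antigen does not alter the result.

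This rests on three assumptions: that section 3.7 implies a formal test, that the table's 20 IU/ml scoring stands, and that its 234 children are the relevant analysis set.

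**What to change.** - Restate Hypothesis 1 and sections 1.1, 3.3 and 3.7 in terms of anti-PT and anti-FHA.
- State the criterion: each seroconversion rate is tested against 70% by its lower two-sided 95% limit.
- Allow an overall pertussis claim only if both pass. No alpha split is needed for that claim. If one passes, the conclusion names that antigen only.
- If the sponsor prefers a single primary antigen, name it in advance and confine the claim to it. Day-28 results already stand in Supplementary Table 1, so a choice first made now should be reported as made after the data.
- Reconcile the cut-offs in section 3.3 with those in Supplementary Table 1, and state the table's analysis set.

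**Cost.** The changes are to wording and need no new data. An overall claim becomes harder to meet. With 90% power per antigen, joint power lies between 0.90 + 0.90 − 1 = 80% and 90%, or 0.90 × 0.90 = 81% under independence. The 90% in section 3.7 should therefore be stated as per antigen, and on that footing no extra participants are needed. Single-antigen claims at the unadjusted level also carry some multiplicity. If both true rates were 70%, the chance of at least one false claim would be about 1 − (1 − 0.0236)² = 4.7% under independence, against 2.4% for one antigen. The text should acknowledge this.

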## 1. STUDY OBJECTIVE

### 1.1. Primary objective

The primary outcomes of the study were the seroconversion rates and seropositive rates of anti-pertussis antibodies in the co-purified DTaP group, as well as a comparison of seroconversion rates and seropositive rates of anti-diphtheria and anti-tetanus antibodies in the co-purified DTaP and DT groups.

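### Hypothesis 2 frames the diphtheria and tetanus goal as no significant difference, with no margin or interval rule, so read literally a real deficit can support it and a better DTaP response contradicts it

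*Combined protocol and SAP*

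**What the plan says.** The Hypotheses row of the protocol synopsis holds two statements. The first is "The seroconversion rate of pertussis antibody in 6-year-old children vaccinated with co-purified DTaP vaccine is not less than 70" per cent. The second is "There was no significant difference in the seroconversion rates of diphtheria and tetanus antibodies" between children given DTaP and children given DT. The first is plainly a result the trial hopes to show, so the natural reading of the second is also a goal, not a null to be rejected.

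Section 1.1 puts the between-arm result among the primary outcomes: "as well as a comparison of seroconversion rates and seropositive rates of anti-diphtheria and anti-tetanus antibodies". Section 1.2 repeats the same text as secondary.

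The only between-arm test named is in the footnote to Supplementary Table 1, a results table outside the protocol body: a two-sided chi-square "test or Fisher's exact test to compare seroconversion rates between arms".

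Section 3.7 sizes the trial on pertussis alone: "Assuming the target value was 70% of the seroconversion rate of anti-pertussis in the co-purified DTaP group". It states no power for diphtheria or tetanus. The available text contains no non-inferiority or equivalence margin, no direction and no confidence-interval criterion for this comparison.

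**The concern.** A non-significant difference test does not show that two rates are similar; it may only show that the data are imprecise. If "There was no significant difference" is the target, fewer evaluable children make it easier to reach, because the same true deficit is then less likely to be detected. The rule also has no direction. A clear DTaP advantage is a significant difference, so it counts against the hypothesis.

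At stake is whether a diphtheria or tetanus response no worse than with DT can be claimed for DTaP. As worded, the hypothesis can support that claim when it is false and withhold it when DTaP does better.

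**Working it through.** **Inputs.** 240 per arm, 15% loss, two-sided alpha 0.05 (section 3.7): 240 × 0.85 = 204 evaluable per arm. Two-sided chi-square test (Supplementary Table 1 footnote). The documents give no planning rates for diphtheria or tetanus and no margin, so the rates and margins in steps 2 and 4 are assumptions.

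**1. The plan's own figure.** The expected pertussis rate is not stated, so 240 cannot be derived from the stated inputs alone. Assuming 80% against the 70% target:

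n = [1.96√(0.7×0.3) + 1.2816√(0.8×0.2)]² / 0.10² = 199.04, rounded up to 200; 200/0.85 = 235.3, rounded up to 236.

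This is close to 240, so the number is plausible for the pertussis criterion. It says nothing about the DTaP–DT comparison.

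**2. Chance that a real deficit is non-significant.** For n per arm, sum Bin(x; n, p_DT) × Bin(y; n, p_DTaP) over all pairs with |z| < 1.96, where z = (y − x)/n ÷ √(2p̄(1−p̄)/n) and p̄ = (x + y)/(2n).

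| True DTaP vs DT | Deficit | Non-significant, n = 204 |
|---|---|---|
| 90% vs 95% | 5 points | 52% |
| 85% vs 90% | 5 points | 67% |
| 82.1% vs 87.1% | 5 points | 72% |
| 95% vs 100% | 5 points | 0.8% |
| 85% vs 95% | 10 points | 7% |
| 80% vs 90% | 10 points | 19% |

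Hand check for 90% vs 95%: the null standard error is √(2×0.925×0.075/204) = 0.0261 and the alternative one is √((0.95×0.05 + 0.90×0.10)/204) = 0.0260. Power = Φ((0.05 − 1.96×0.0261)/0.0260) = 0.483, so about 52% are non-significant.

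With only 100 per arm, the figures for 90 vs 95, 85 vs 90 and 80 vs 90 rise to 73%, 81% and 48%. Losing data makes the hypothesis easier to meet.

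**3. The other direction, from the reported counts.** Summing the two baseline strata of Supplementary Table 1 (split at 0.1 IU/ml):

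- Tetanus: DTaP (207+20)/(214+20) = 227/234 = 97.0%; DT (174+21)/(203+21) = 195/224 = 87.1%. The difference is +10.0 points; Fisher P = 0.00008. Wilson limits are 93.96–98.54% and 82.03–90.83%. Newcombe lower limit: 9.95 − √(3.05² + 3.78²) = +5.1. Upper limit: 9.95 + √(1.53² + 5.03²) = +15.2.
- Diphtheria: 234/234 vs 224/224. The difference is 0, with 95% CI −1.6 to +1.7 points.

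Tetanus is significantly different in favour of DTaP, so Hypothesis 2 as worded is not met. Both lower limits lie above −5 and −10 points.

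**4. What a non-inferiority rule would give with 204 per arm.** With equal true rates p and margin M, power = Φ(M/√(2p(1−p)/204) − 1.96). At p = 90% and M = 10 points: 0.10/0.0297 = 3.367, and Φ(1.407) = 0.92.

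| Common rate | Margin −10 | Margin −5 |
|---|---|---|
| 85% | 81% | 29% |
| 90% | 92% | 39% |
| 95% | 99.6% | 64% |

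Requiring both antigens at 90% and −10 points gives 0.92² = about 85% if the two are independent.

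**The case against.** The strongest reply is that this is one loosely worded line. The protocol text never says that a non-significant P will be taken as success or confirmation, and the two-sided test appears only under a results table. Hypothesis 2 might be a badly phrased null, section 1.1 asks only for a comparison, and the synopsis objective concerns pertussis. Not every part of the protocol was available for review, and a margin could be stated elsewhere.

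Much of this stands. A reader might infer that the plan explicitly declares success on a non-significant test; the documents do not say so. It is the literal consequence of a listed hypothesis with no other rule in view. Reading it as a null is less natural beside Hypothesis 1. A margin stated elsewhere would conflict with the synopsis, which would still need correcting.

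Two further limits stand. The false-pass figures depend on the control rate and should not be carried over to both antigens: with DT at 100%, as reported for diphtheria, a 5-point deficit is almost always detected. The tetanus example also rests on strata summed here and on the table's 0.1 IU/ml cut-off, whereas section 3.3 gives 20 IU/mL for diphtheria and tetanus and 0.1 IU/mL for pertussis, the reverse of the table. The example therefore does not use the endpoint as section 3.3 writes it.

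**Conclusion.** The point holds for the wording and the missing decision rule. As written, Hypothesis 2 can be supported by a real deficit and contradicted by an advantage. At 204 per arm the first risk is 52% to 67% for a 5-point deficit from an assumed control rate of 95% or 90%, and 7% to 19% for a 10-point deficit. It is under 1% for a 5-point deficit from 100%. The second is shown by the reported tetanus counts, subject to the cut-off conflict.

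Two stronger readings are not supported. The tetanus result is no evidence against DTaP; its lower limit of +5.1 points favours DTaP. Nor is 240 per group shown to be wrong: it was set for the pertussis criterion and is plausible there. Because sections 1.1 and 1.2 list the same comparison as both primary and secondary, its standing also needs settling. The finding is limited to the text available for review.

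**What to change.** First reconcile the antibody cut-offs in section 3.3 with those in Supplementary Table 1, since the endpoint depends on them.

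Then replace Hypothesis 2 with non-inferiority of DTaP to DT for each antigen. The criterion is that the lower limit of the two-sided 95% CI (Newcombe or Miettinen–Nurminen) for DTaP minus DT in D28 seroconversion lies above a margin that the sponsor justifies. Require both antigens. Report superiority for an antigen if its lower limit exceeds 0. Keep the PPS primary, as section 6 has it, with the FAS supportive; state how missing D28 titres are handled there, because FAS entry needs only a valid pre-immunization titre. Say whether the rule also covers the seropositive rates named in section 1.1.

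Results already exist, so a margin set now must be labelled post hoc. The reported lower limits (+5.1 and −1.6 points) mean the conclusion would not turn on a choice between 5 and 10 points, subject to the cut-off question.

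For this trial the cost is wording and a margin justification. For planning it depends on the margin and rates. For 90% power per antigen after 15% loss, a −10 point margin needs 118 per arm at 95%, 224 at 90% and 316 at 85%, so 240 suffices only at about 90% or above, and joint power is lower. A −5 point margin at 90% would need 891 per arm.
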